## 1.6 RESEARCH HYPOTHESIS

The research hypothesis of this study is:

- H1:** The sociodemographic, socioeconomic, working experience, and training attendance characteristics of the intervention and control groups would be the same.
- H01:** There is no significant differences in the sociodemographic, socioeconomic, working experience, and training attendance characteristics of the intervention and control groups.
- H2:** The KAP on occupational safety and health at food premises of the intervention and control groups at the baseline would be the same.
- H02:** There is no significant differences in the KAP on occupational safety and health at food premises of the intervention and control groups at the baseline.
- H3:** The SCT constructs as the main framework of the intervention module is effective in improving KAP among food handlers between the intervention and control group.
- H03:** The SCT constructs as the main framework of the intervention module have no significant effect in KAP among food handlers between the intervention and control group.
- H4:** The TRIM-OSH effectively improves KAP on occupational safety and health at food premises among food handlers.

**H04:** There is no significant differences in the KAP on occupational safety and health at food premises of the intervention and control groups at post-intervention.

## CHAPTER 2

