### **3.2 Study design**

The study is a randomized controlled trial study. A single blinded, cluster randomized controlled trial study design will be conducted with pre-assessment and post-assessment on the intervention module. The respondents will be divided into two groups, intervention or control. The control group will receive a standard treatment and brochures related to occupational safety and health, while the intervention group will receive a theory-based intervention module on occupational safety and health among food handlers. The duration of the study is within 3-6 months.

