### 3.5 Sampling technique

There are 324 Food Handler Training Schools in Selangor located in nine districts. This study will use a simple random sampling technique to select the sampling location. Four districts will be randomly selected. Once the district is determined, the selection of the Food Handler Training School within the district will proceed by using a similar method and subsequently assigned. The flow of the sampling technique is shown in the figure below:

[figure not shown]

Figure 5. Cluster random sampling flow chart.

Cluster randomization will be used to ensure administrative efficacy, lessened risk of experimental contamination, and enhancement of subject compliance. The participants attending the food handler training program will be invited into the study via invitation and assessed for eligibility. The unit of randomization will be on a 1:1 basis in either the control or intervention group.

An independent research staff, blinded as to whether they were nominating within the control or an intervention group and unaware which of their participants had consented to participate.

[figure not shown]

Figure 6. Proposed research Flow Chart

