### 3.6 Sample size

The sample size calculation in this study was based on the targeted primary outcomes, such as knowledge, attitude, and practice of safety and health. A previous power analysis specified an enrolment target of 20 clusters of six participants per condition. Provided that the average attrition rate in previous intervention studies was 20%, conservative estimation will be conducted on the attrition at 20% for each testing time point when the target sample size is designed. Given that the total time points in this study requirement are three times follow up after the baseline data collection, the required sample size comprises 20 clusters of 12 participants per group ( $N = 240$ ). To encourage retention, lottery-style drawings will be carried out for participants who complete each data

collection phase. Retention bonus pay will be offered for those who complete all four data collection phases.

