All results of log-transformed data considered underlying data transformation in result interpretation. The confidence interval will be set at 95% for mean estimations. The level of significance, alpha ( $\alpha$ ), will be set at 0.05. A p-value of less than 0.05 pertained to the decision rule. The dependent variables measured in this study are the outcome (primary and secondary) and effectiveness of the SCT constructs as the base of theory-based intervention module in occupational safety and health training among food handlers.

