| Government servant                    |                            |              |                  |         |
| Private company                       |                            |              |                  |         |
| Self-employed                         |                            |              |                  |         |
| Student                               |                            |              |                  |         |
| Unemployed                            |                            |              |                  |         |
| Monthly individual income (RM) |                            |              |                  |         |
| Monthly household income (RM)  |                            |              |                  |         |
| Previous working experience    |                            |              |                  |         |
| Yes                                   |                            |              |                  |         |
| No                                    |                            |              |                  |         |
| Length of experience (years)   |                            |              |                  |         |
| Previous training attendance   |                            |              |                  |         |
| Yes                                   |                            |              |                  |         |
| No                                    |                            |              |                  |         |
| Typhoid injection status       |                            |              |                  |         |
| Yes                                   |                            |              |                  |         |
| No                                    |                            |              |                  |         |

Table B. Between-group difference of total score of self-efficacies, behavioral capacity, and supportive working environment on occupational safety and health at food premises.

|                                                          | Group median (IQR) |                   |         |
|----------------------------------------------------------|--------------------|-------------------|---------|
|                                                          | Baseline           | Post-intervention | 1-month |

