| The total score of self efficacies                |                    |                   |         |
| Control                                                  |                    |                   |         |
| Intervention                                             |                    |                   |         |
| Man-Whitney U Test                                       |                    |                   |         |
| p-value                                           |                    |                   |         |
| The total score of behavioral capacity            |                    |                   |         |
| Control                                                  |                    |                   |         |
| Intervention                                             |                    |                   |         |
| Man-Whitney U Test                                       |                    |                   |         |
| p-value                                           |                    |                   |         |
| The total score of supportive working environment |                    |                   |         |
| Control                                                  |                    |                   |         |
| Intervention                                             |                    |                   |         |
| Man-Whitney U Test                                       |                    |                   |         |
| p-value                                           |                    |                   |         |

Significant at  $p < 0.05$

Table C. Within intervention group difference of total score of self-efficacies on occupational safety and health at food premises.

| Self-efficacy on occupational safety and health at food premises | Mean $\pm$ SD | F* | p-value** |
|------------------------------------------------------------------|---------------|----|-----------|
| Within Intervention group.                                       |               |    |           |
| Baseline                                                         |               |    |           |
| Post-intervention                                                |               |    |           |
| 1-month                                                          |               |    |           |

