| Within Control Group                                             |               |    |           |
| Baseline                                                         |               |    |           |
| Post-intervention                                                |               |    |           |
| 1-month                                                          |               |    |           |

\*Repeated measure ANOVA

\*\*Bonferroni adjustment

\*\*\*Significant at  $p < 0.05$

Table D. Within intervention group difference of total score of behavioral capacity on occupational safety and health at food premises.

| Behavioral capacity on occupational safety and health at food premises | Mean $\pm$ SD | F* | p-value** |
|------------------------------------------------------------------------|---------------|----|-----------|
| Within Intervention group.                                             |               |    |           |
| Baseline                                                               |               |    |           |

|                      |  |  |  |
|----------------------|--|--|--|
| Post-intervention    |  |  |  |
| 1-month              |  |  |  |
| Within Control Group |  |  |  |
| Baseline             |  |  |  |
| Post-intervention    |  |  |  |
| 1-month              |  |  |  |

\*Repeated measure ANOVA

\*\*Bonferroni adjustment

\*\*\*Significant at  $p < 0.05$

Table E. Within intervention group difference of total score of supportive working environment on occupational safety and health at food premises.

| Supportive environment on occupational safety and health at food premises | Mean $\pm$ SD | F* | p-value** |
|---------------------------------------------------------------------------|---------------|----|-----------|
| Within Intervention group.                                                |               |    |           |
| Baseline                                                                  |               |    |           |
| Post-intervention                                                         |               |    |           |
| 1-month                                                                   |               |    |           |
| Within Control Group                                                      |               |    |           |
| Baseline                                                                  |               |    |           |

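### The dummy results tables omit knowledge, attitude and practice, and their tests of the SCT constructs do not fit a cluster-randomised comparison

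*Combined protocol and SAP*

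**What the plan says.** Section 3.2 sets the design: "A single blinded, cluster randomized controlled trial study design will be conducted with pre-assessment and post-assessment on the intervention module". Section 3.5 adds "The unit of randomization will be on a 1:1 basis in either the control or intervention group". The primary outcomes in section 3.6.1 are change in knowledge and change in attitude; practice is secondary. H2 to H4 in section 1.6 all concern KAP. H3 reads "The SCT constructs as the main framework of the intervention module is effective in improving KAP among food handlers between the intervention and control group", and H04 is a between-group null after the intervention.

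Section 3.10 plans a generalised linear mixed model (GLMM) on KAP, within and between groups, and a further analysis of the SCT constructs on KAP. The random effects it describes are a subject intercept and a subject slope. On significance it says "A p-value of less than 0.05 pertained to the decision rule".

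The dummy tables in section 4.1 show the following:

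- Table A compares baseline characteristics.
- Table B is headed "Table B. Between-group difference of total score of self-efficacies, behavioral capacity, and supportive working environment on occupational safety and health at food premises". It has a Mann-Whitney row for each of three scores at baseline, post-intervention and one month.
- Table C is headed "Table C. Within intervention group difference of total score of self-efficacies on occupational safety and health at food premises". Tables D and E repeat its layout for the other two constructs. Each lists the intervention and control arms separately, with the footnote "Repeated measure ANOVA" and a Bonferroni note.
- Table F lists coefficients with standard errors and 95% confidence intervals for self-efficacy. Its rows are Group, Time and Education.

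No visible table reports a knowledge, attitude or practice score.

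**The concern.** Dummy tables fix what will be reported. These leave out the primary outcomes and give the space to construct scores. The tests they name are also a poor match for the design. Table B treats participants as independent although they are allocated in clusters. Tables C to E test change within each arm, and since both arms receive training and are retested, both may improve. Table F has no term that isolates a difference in change. Section 3.10 names neither the Mann-Whitney test nor repeated-measures ANOVA, so the tables and the analysis text describe different analyses. If the tables were filled in as drawn, the reported p-values for the constructs would be too small, and the KAP comparison that H4 and Objective 4 require would have no place in the results.

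**Working it through.** **Inputs from the documents.** Section 3.6 starts from "A previous power analysis specified an enrolment target of 20 clusters of six participants per condition", assumes 20% loss at each time point over three follow-ups, and arrives at clusters of 12 with N = 240. The nominal level is 0.05 (section 3.10), taken here as two-sided because sidedness is not stated. Table B covers three scores at three times.

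**Assumption.** The documents give no intracluster correlation (ICC). I use 0.01 to 0.10.

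**Step 1: the plan's own figure.** 6/0.8^3 = 11.72, rounded up to 12 per cluster; 20 x 12 = 240. This reproduces N if 20 is the trial total. If 20 were the number in each arm, N would be 480. The Executive Summary gives 139, which does not follow from these inputs. The underlying power calculation cannot be checked, because no effect size, SD, ICC or power is stated.

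**Step 2: Table B and clustering.** For cluster size m, the design effect is DE = 1 + (m - 1) x ICC. A test that ignores it has approximate error 2 x (1 - Phi(1.96/sqrt(DE))). With m = 12:

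| ICC | DE | Type I error, formula | Mann-Whitney, simulated |
|---|---|---|---|
| 0.01 | 1.11 | 0.063 | 0.059 |
| 0.05 | 1.55 | 0.115 | 0.109 |
| 0.10 | 2.10 | 0.176 | 0.172 |

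The simulation used 10 clusters per arm and 4000 runs per setting; at ICC = 0 it gave 0.050. Section 3.5 selects four districts and does not say how many schools. If there were only four clusters of about 35 (one school per district, total 139, a further assumption), the formula gives 0.090, 0.233 and 0.350 at the same three ICCs.

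**Step 3: Table B and multiplicity.** Of 3 x 3 = 9 tests, three are at baseline, leaving six that bear on efficacy. At 0.05 each, 1 - 0.95^6 = 0.265 if they are independent. Positive correlation between the scores would lower this. The figure takes each test at its nominal level, before the inflation in step 2.

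**Step 4: Tables C to E.** H04 concerns a difference between arms. Each F test in these tables uses one arm only, so no pair of them estimates that difference. The Bonferroni note adjusts within an arm and does not change this.

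**Step 5: Table F.** With Group and Time but no Group x Time, balanced data and equal baselines, the Group coefficient is the mean of the three wave-specific differences. For a true difference d at both post-baseline waves this is (0 + d + d)/3 = 2d/3. With d = 0.50 it is 0.33; a simulation of 500 trials gave 0.331.

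**Step 6: the model in section 3.10.** It names subject-level random effects only. It has no effect for the unit of randomisation and writes out no Group x Time contrast. Filling the tables from it as written would therefore still leave the clustering unaddressed.

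**The case against.** The strongest reply is that dummy tables are a template and section 3.10 is the analysis. That section plans a KAP model within and between groups and a separate analysis of the constructs on KAP. The Executive Summary ties the GLMM to the effect of TRIM-OSH on KAP, and Objective 4 asks for covariate-adjusted change. This stands. A reader might infer from the tables that the plan contains no KAP analysis, or no analysis of H3 or H4; the documents do not support that. The defect is that the tables do not match the text. One page between Table F and the references is also absent from the text reviewed. The contents list suggests it is the acknowledgements, so the statement about KAP is limited to the visible tables.

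Three further points on that side hold:

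- Table B does compare the randomised arms directly. Leaving out baseline and covariates mainly costs precision; ignoring clustering is what damages validity.
- Within-group change is a stated aim of Objective 4, so Tables C to E have a place as description. A reader might infer that effectiveness will be declared when the intervention arm is significant and the control arm is not. The plan states no such rule, and any error rate attached to it would need assumed powers.
- Repeated-measures ANOVA normally uses complete cases, and 0.8^2 = 64% would remain after two follow-ups at the planned loss. Reading that as loss caused by the ANOVA goes too far: most of it is dropout that any analysis faces.

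None of this answers the clustering in Table B, the missing interaction in Table F or the absence of KAP tables.

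**Conclusion.** The visible dummy tables do not carry the KAP model of section 3.10, and the tests they name do not fit the design. Table B's type I error is about 0.06 to 0.18 for clusters of 12, resting on an assumed ICC of 0.01 to 0.10, and it would be higher with fewer, larger clusters. Its six efficacy tests are uncorrected, with familywise error about 0.27 under independence. Tables C to E can describe change but cannot test H04. Table F, the only model-based arm comparison shown, covers one construct and would report about two thirds of a constant post-baseline effect. The missing tables and terms are plain from the text; only the size of the error inflation depends on figures the documents do not give.

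**What to change.** Put tables for knowledge, attitude and practice first, followed by the three constructs. Each should show means by arm and time, and the adjusted between-arm difference with its 95% confidence interval at post-training and at one month. Take these from one mixed model with Group x Time, the listed covariates, a subject random effect and an added random effect for the unit of randomisation. Section 3.5 reads as allocating schools, but the plan should say so. Include a small-sample correction for few clusters.

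Remove the Mann-Whitney p-values from Table B and add Group x Time to Table F. Label Tables C to E descriptive, with no inference about efficacy; this still meets the within-group part of Objective 4. Keep H3, because rewording it would change the question in Objective 3. State that between-arm comparisons of construct scores show only whether the module moves the constructs, and keep the analysis of constructs on KAP separate from the model that estimates the TRIM-OSH effect.

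The cost is a model amendment as well as redrafted tables, and wider confidence intervals once clustering is included. No new data are needed.

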**INTERVENTION MODULE OUTLINE**

**FIRST SESSION (1 HOUR)**

**MAIN OBJECTIVE:**

1. To enhance self efficacy among food handlers on occupational safety and health at food premise

**SPECIFIC OBJECTIVE:**

1. To introduce food handlers on common type of hazards at food promises
2. To introduce food handlers on common occupational safety and health issues among food handlers
3. To educate food handlers on safe working environment at food premises
4. To emphasize on role of employer and employee in regards of occupational safety and health at food premise
5. To educate food handlers on appropriate risk assessments and risk controls towards identified hazards at food premises

**CONTENT OUTLINE:**

1. Type of hazards
2. Role of employer and employee
3. Safety and health issues
4. Safe working environment
5. Hazards identification
6. Risk assessment
7. Risk control

**MODE OF DELIVERY:**

1. Web-based online course
2. Power point presentation
3. Video demonstration
4. Quiz

**SECOND SESSION (1 HOUR)****MAIN OBJECTIVE:**

1. To potrait supportive working environment on occupational safety and health at food premises among food handlers

**SPECIFIC OBJECTIVE:**

1. To instill the importance of shared responsibility between employer, employee, and governmental agency in ensuring supportive working environment towards occupational safety and health at food premises
2. To emphasize the role and importance of an effective training for food handlers in preventing occupational injury and illnesses

**CONTENT OUTLINE:**

1. Role and responsibility of the employee, employer, and governmental agencies.
2. Role of occupational safety and health training for food handlers
3. The effectiveness of TRIM-OSH in preventing occupational injury and illnesses
4. The importance of occupational safety and health training for food handlers

**MODE OF DELIVERY:**

1. Web-based online course
2. Power point presentation
3. Video demonstration
4. Quiz

**THIRD SESSION (1 HOUR)****MAIN OBJECTIVE:**

1. To increase behavioral capabilities on occupational safety and health practices among food handlers at food premises

**SPECIFIC OBJECTIVE:**

1. To impart knowledge on safe practices while working at food premises based on given circumstances
2. To demonstrate on skills to perform correct safe practices based on given work activity

